***Inclusion criteria***

 Aged 65 or older at baseline Rockwood clinical frailty scale score 4 or 5 (vulnerable or mildly frail) Able and willing to provide informed consent and to comply with the requirements of this study protocol

***Exclusion criteria***

 Rockwood clinical frailty scale score > 5 End of life care Persons in residential care home Concurrent malignancyChronic kidney disease, stage 3 or 4 Coded diagnosis of severe dementia as per GP or consultant geriatrician diagnosis or baseline Montreal Cognitive assessment (MoCA) score ≤ 10 Persons unable to engage in discussion on frailty due to acute care needs or determined to be inappropriate by GP (e.g., needing transfer to ED or acutely unwell or disorders resulting in intolerance of the intervention) Subjects unable to provide written informed consent

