### Benefits and risks

The systematic review
^6^ identified benefits to patients that include decreased risks of illnesses, falls, dependency, disability and improved mortality. 71% of studies measuring impact on frailty status demonstrated significant improvement. 69% of studies measuring impact on singular frailty indicators or other criteria demonstrated significant improvement. The exercises create a small risk of musculoskeletal strain. No such adverse event was recorded during a feasibility study of the intervention, prior to PPI optimisation. The risk was mitigated by the fact that the exercises are simple in nature and the supporting patient information leaflet advises thirty second breaks between exercises and not to undertake any exercise that causes pain. Risk is further mitigated by excluding participants with CFS 6 and above. The risk (probability) of harm is considered to be low.

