### Selection of study population

All patients aged 65 or older attending the GP site investigator will be screened for eligibility by the GP. Patients meeting all of the inclusion criteria and none of the exclusion criteria will be eligible for inclusion.

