## Intervention

### Description of intervention

The resistance exercise regime consists of ten, home-based, physical exercises as illustrated in an accompanying leaflet. Each exercise is to be repeated ten times in one minute, increased to fifteen times per minute after about 1 month, when comfortable. A break of 30 seconds is to be taken between sets of exercises. Exercises are to be undertaken at least four times per week and up to every day. Participants should also walk for 30 to 45 minutes, three to four times per week. Participants are advised to consume 1.2 g protein per kg body weight each day. A leaflet will be provided with information on sources of protein, amounts of protein per typical serving and suggested meals. A sample exercise leaflet and protein dietary guidance are shown in
Figure 4 and
Figure 5.

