### Determination of sample size subjects

We have calculated a sample size of 176 with the following parameters: Two independent study groups (i.e., control and intervention); outcome measure of frailty status (i.e., change from frail or pre-frail to non-frail as measured by SHARE-FI); improvement of frailty status in the intervention group to non-frail of 15%, allowing for a 3% improvement in the control group due to bias; enrolment ratio of 1; probability of type I error of 5% (0.05); power 80%. Enrolment of 210 participants assumes a 15% drop out rate.

Sample sizes in comparable trials include Binder, J Am Geriat Soc 2002 (sample size 115)
^20^, Liu, Clin Rehab 2017 (sample size 79)
^21^ and Serra-Prat, Age Aging 2017 (sample size 172)
^2^. The average study size of the 31 studies included in our meta-analysis of frailty interventions
^7^ was exactly 100.

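### The renal exclusion names CKD stages 3 and 4 only, so as worded it bars milder disease but not stage 5 or dialysis

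*Protocol article*

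**What the plan says.** Under Selection of study population, the protocol article makes eligibility depend on the two lists: "Patients meeting all of the inclusion criteria and none of the exclusion criteria will be eligible for inclusion".

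The inclusion list asks for age 65 or over, informed consent with willingness to comply, and a frailty grade given as "Rockwood clinical frailty scale score 4 or 5 (vulnerable or mildly frail". It sets no renal condition.

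The exclusion list contains one renal line, printed in the extracted text as "Concurrent malignancyChronic kidney disease, stage 3 or 4". The missing break between malignancy and kidney disease comes from text extraction and does not affect the stages named.

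Two other exclusions could bear on a patient with advanced kidney disease. One is "End of life care". The other covers people whose acute needs prevent a discussion of frailty, and also anyone "determined to be inappropriate by GP (e.g., needing transfer to ED or acutely unwell or disorders resulting in intolerance of the intervention".

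Description of intervention states the dietary component: "Participants are advised to consume 1.2 g protein per kg body weight each day". Benefits and risks discusses musculoskeletal strain from the exercises and adds: "Risk is further mitigated by excluding participants with CFS 6 and above".

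**The concern.** A criterion based on disease stage normally excludes everything from a threshold to the severe end. This one names two stages and stops. In the usual staging, where a higher number means more severe disease, stage 5 lies beyond both. The stated rule therefore bars a person with stage 3 disease and does not, on renal grounds, bar the same person with stage 5 disease. No reason is given for treating stage 5 differently.

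This is not a detail left to a fuller document. The article states the criterion with explicit stage numbers, and the rule as stated runs the wrong way at its severe end.

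What is at stake is participant protection and a screening rule that seven practices can apply as intended. A person whom the criterion was presumably meant to keep out could be randomised and, in the intervention arm, given the daily protein target. No estimate, error rate or power figure is at stake.

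**Working it through.** **1. Apply the rule to two people.** Take two community-dwelling patients aged 65 or over, both CFS 4 or 5, both able to consent, and differing only in kidney disease.

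| Criterion | CKD stage 3 | CKD stage 5 |
|---|---|---|
| Inclusion criteria | met | met |
| Renal exclusion | excluded | not excluded |
| End-of-life care exclusion | not triggered by stage alone | not triggered by stage alone |
| GP judgement of inappropriateness | not needed | may exclude, at the GP's discretion |

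The milder case is settled by a fixed rule. The more severe case is left to judgement.

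**2. Compare with the other limits in the same list.** The frailty exclusion covers every CFS score above 5. The cognitive exclusion covers every MoCA score of 10 or below. Both run open to the severe end; the renal line does not. This makes a drafting slip the most plausible reading, though the article does not confirm it.

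**3. Size.** The article gives no CKD prevalence. Assume that 0.2% to 1% of those enrolled would have stage 5 disease, before any exclusion by the GP:

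- all enrolled: 0.002 × 210 = 0.42, and 0.01 × 210 = 2.1, so about 0 to 2 people;
- intervention arm under 1:1 allocation: 0.42 / 2 = 0.21, and 2.1 / 2 = 1.05, so about 0 to 1 person.

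**4. Does the design depend on it?** The inputs under Determination of sample size subjects are "improvement of frailty status in the intervention group to non-frail of 15%, allowing for a 3% improvement in the control group due to bias", with 1:1 allocation, 5% type I error and 80% power. With a two-sided test, pooled variance and no continuity correction:

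n per arm = [1.960 × √(2 × 0.09 × 0.91) + 0.842 × √(0.15 × 0.85 + 0.03 × 0.97)]² / 0.12² = (0.793 + 0.333)² / 0.0144 ≈ 88.1, rounded up to 89.

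That is 178 in total, against 176 stated. The unpooled form gives 86 per arm, or 172. Power at 88 per arm is 0.7996. Allowing for 15% dropout, 176 / 0.85 = 207.1, or 208 rounded up, against 210 stated. The stated figures reproduce closely, and kidney disease is not an input to any of them. Extending the exclusion to stage 5 leaves them as they are.

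**The case against.** The strongest reply is that the list has a backstop. The GP may exclude anyone judged inappropriate, and the reasons in that clause are examples, not limits. The attending GP screens every patient, so a GP who knows of stage 5 disease may well decline to enrol. Further protection is available after enrolment. The withdrawal section requires discontinuation for any medical condition that the investigator or sponsor considers a danger to the subject. Comorbidities are recorded at baseline, GPs are trained and meet monthly, and intervention participants are telephoned at one month and asked about the diet.

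This stands as far as it goes, and it rules out several stronger statements that a reader might infer:

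- *A stage 5 patient passes every listed criterion.* Not supported. The GP-judgement clause is itself a listed criterion and may exclude the patient.
- *Eligibility is the only renal safeguard.* Not supported, given the safety-withdrawal rule and the contacts above.
- *The advice carries no renal caution.* This cannot be known. The dietary leaflet is Figure 5, which is not shown.
- *Sites would withdraw such patients inconsistently.* This is speculation. On the literal reading the patient is not ineligible on renal grounds, and the training is meant to standardise practice.
- *The advice is a high-protein diet that harms these patients.* The article describes protein within a normal balanced diet, gives no reason for the renal exclusion and offers no evidence of harm at this intake. The link between the exclusion and the protein advice is an inference.

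None of this repairs the criterion. The discretionary provisions do not name renal disease, and the withdrawal rule acts only after enrolment. The authors chose a fixed rule for stages 3 and 4, and nothing suggests that they meant to rely on discretion for the more severe stage.

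**Conclusion.** The concern holds in limited form. The renal exclusion is a closed list that omits stage 5 and dialysis, so the fixed rule is stricter for milder disease than for the most severe. Discretionary provisions can still catch such a patient but do not replace the missing stage.

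The size is about 0 to 2 of 210 enrolled, and about 0 to 1 in the intervention arm. This rests on an assumed prevalence of 0.2% to 1%, applied to enrolled participants with no GP exclusion, so it probably errs high within that assumption. Sample size, power and the primary analysis are untouched. The case for acting is a plain gap in a protective criterion that costs almost nothing to close. It does not rest on any demonstrated harm or on an effect on the trial's results.

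**What to change.** In Exclusion criteria, and in the matching line of the screening form, replace the renal criterion with: *Chronic kidney disease, stage 3 or above (including dialysis)*. Print it as its own item, separate from malignancy.

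The cost is one line in a protocol amendment submitted to the research ethics committee, and one line in the screening form. Few or no participants are affected, and neither the sample size nor the analysis needs to change.

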### Study methods, assessments and procedures

GP site investigators will undergo three team-based training sessions prior to enrolment, monthly meetings after enrolment and additional ad-hoc meetings when required, led by the principal investigator, in order to standardise the approach and align to this study protocol, including patient communication, intervention delivery and data gathering and management.

Adults attending a GP surgery, meeting the eligibility criteria, will be offered general information about the study by the attending GP. If interested and willing to consent, they will be offered an information leaflet for the trial, and invited to participate. Participants will be randomly assigned to ‘intervention’ or ‘usual care’ parallel arms.

Participants randomly assigned to the usual care group will receive normal primary care, including physical rehabilitation if needed.

Intervention participants will be provided a leaflet with strength exercises and a discussion on how strength exercises have been shown to delay and reverse frailty and build resilience. The information leaflet will have a photographic overview of a home-based exercise regime. They will also be provided with information on post exercise protein consumption as part of a normal balanced diet.

Baseline measurements for all recruited patients will be: age, sex, education, living arrangement (alone, with others), smoking status, alcohol intake, blood pressure, heart rate, BMI (weight and height), comorbidities, malnutrition universal screening tool (MUST), CFS, SHARE-FI (which includes handgrip strength) and bioelectrical impedance for muscle mass, body fat, bone weight, base metabolic rate and ‘biological age’. Bioelectrical impedance will be measured using a Tanita RD 545 Segmental Body Composition Analyser, with dual frequency technology and medical grade accuracy.

Intervention participants will be called after one month and after three months by the GP and asked if they had followed the exercise regime (and for how long and how many times a week) and dietary guidance. At three months they will be asked if they found the exercises ‘very easy’, ‘somewhat easy’, ‘neither easy nor hard’, ‘somewhat hard’, or ‘very hard’; and had they noticed any subjective difference to their health as a result of the intervention, namely feeling ‘much better’, ‘slightly better’, ‘about the same’, ‘slightly worse’ or ‘much worse’. All participants will be invited to return at three months for a clinical assessment and measurement of health indicators and frailty status as described above by the GP. Participants will be invited to return for subsequent one year follow up appointments. This 12-month follow up will be subject to a further ethics committee review. The follow up visits will be free of charge. A schedule of events for baseline, one-month call and three months follow up are shown in
Figure 3.

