## Safety reporting

Participants are asked not to undertake any exercise that causes pain and to discontinue the exercise regime if they have any concern, injury or physical signs constraining participation. Safety will be evaluated throughout the study by recording adverse events (AEs), and inviting participants to attend for assessment of vital signs and physical exam, should they contact their GP with any concerns.

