### Reporting procedures for all adverse events

All AEs occurring during the study observed by the investigator or reported by the subject, whether or not attributed to the study medication, will be documented.

The following information will be recorded: description, date of onset and end date, severity, assessment of relatedness to the study intervention, other suspect medication or device and action taken. Follow-up information should be provided as necessary.

AEs considered related to the study intervention as judged by an investigator will be followed until resolution or until the event is considered stable. All related AEs that result in a subject’s withdrawal from the study or are present at the end of the study, should be followed up until a satisfactory resolution occurs.

It will be left to the investigator’s clinical judgment whether or not an AE is of sufficient severity to require the subject’s removal from the study. A subject may also voluntarily withdraw due to what he or she perceives as an intolerable AE. If either of these occurs, the subject must undergo an end-of-study assessment and be given appropriate care under medical supervision until symptoms cease or the condition becomes stable.

The severity of events will be assessed on the following scale: mild, moderate, severe.

The relationship of AEs to the study intervention will be assessed by the investigator.

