### Safety analysis

Incidence of in-patient hospitalisation during follow-up and incidence of LTC during follow up will be analysed using a logistic regression model with arm allocation and age as covariates.

All non-serious and serious AEs will be reported in tables in aggregate form by frequency and subjects affected by trial arm.

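### GP calls made only to the intervention arm may inflate its recorded non-serious adverse events in a by-arm table that ignores how events were found

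*Protocol article*

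**What the plan says.** All places are in the protocol article.

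- **Contact in the intervention arm** (Study methods, assessments and procedures): "Intervention participants will be called after one month and after three months by the GP". On these calls they are "asked if they had followed the exercise regime (and for how long and how many times a week) and dietary guidance". The later call adds a rating of ease and asks whether "had they noticed any subjective difference to their health as a result of the intervention", on a scale that includes two grades of feeling worse.
- **Contact in the usual-care arm** (same section): "Participants randomly assigned to the usual care group will receive normal primary care, including physical rehabilitation if needed". No scheduled call is described.
- **Contact common to both arms** (same section): "All participants will be invited to return at three months for a clinical assessment".
- **Participant-initiated route** (Safety reporting): "inviting participants to attend for assessment of vital signs and physical exam, should they contact their GP with any concerns". This is not limited to one arm.
- **What is recorded** (Reporting procedures for all adverse events): the rule covers "All AEs occurring during the study observed by the investigator or reported by the subject". Presumed cause does not matter.
- **How it is reported** (Safety analysis): "All non-serious and serious AEs will be reported in tables in aggregate form by frequency and subjects affected by trial arm". No adverse-event test is stated. Hospitalisation and long-term care admission have their own logistic regression.

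**The concern.** A by-arm adverse-event table can be read as a comparison only if events had a similar chance of being recorded in each arm. Here recording depends on contact with the investigator, and the text gives one arm scheduled contacts that the other lacks. The caller is the GP, who is also the site investigator, so an event mentioned during an adherence call falls within the recording rule. Asking whether and how often someone exercised may well bring out the reason for stopping.

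The events most exposed are mild and moderate ones, such as the musculoskeletal strain named under Benefits and risks, which may go unrecorded unless someone asks. That section calls the probability of harm low, and the Data management committee section gives low risk as one reason for having no external committee. The by-arm table is the randomised evidence on that point. If ascertainment differs, a spurious excess could count against the intervention, and a real excess could be dismissed as a product of extra contact. An analysis plan could not repair this later, because usual-care events that were never recorded cannot be recovered.

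**Working it through.** **Inputs.** The protocol has no figure to reproduce on this point: it gives no adverse-event rate and no detection rate.

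- From the protocol: enrolment of 210 at 1:1, so 210 / 2 = 105 expected per arm; follow-up of three months; calls at one and three months on intervention only; a three-month GP visit in both arms.
- Assumed: true risk of at least one event 20% in both arms; each contact detects a fraction d of events, with d = 0.5 to 0.7; usual care has detection d overall.

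**Which contact is extra.** The three-month call falls close to the three-month visit that everyone is invited to, so it can add little independent detection. The one-month call has no usual-care counterpart, but it cannot detect events that occur in months two and three.

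**Scenario A: the calls recover nothing.** Detection is d in both arms, so the ratio is d / d = 1.0.

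**Scenario B: only the one-month call adds detection, with events spread evenly over three months.** One third of events get a second chance.

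Detection on intervention = d + (1 − d) × d / 3.

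- d = 0.5: 0.5 + 0.5 × 0.5 / 3 = 0.583; ratio 0.583 / 0.5 = 1.17.
- d = 0.7: 0.7 + 0.3 × 0.7 / 3 = 0.77; ratio 0.77 / 0.7 = 1.10.

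**Scenario C (upper bound): one extra independent contact covers all events.**

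Detection on intervention = 1 − (1 − d)².

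- d = 0.5: 0.75; ratio 1.5.
- d = 0.7: 0.91; ratio 1.3.

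**Consequences with 105 per arm.** Recorded risk = 0.20 × detection, and expected participants affected = 105 × recorded risk. The chance that the table shows more affected participants on intervention is an exact calculation from two independent binomials. The last column is the exact two-sided rejection rate of a Pearson chi-square at 0.05. It only illustrates what a reader's own test would do, since the protocol plans none.

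| Scenario | d | Expected affected, intervention v usual care | Ratio | P(more on intervention) | Rejection rate |
|---|---|---|---|---|---|
| A | 0.5 | 10.5 v 10.5 | 1.00 | 0.45 | 0.052 |
| A | 0.7 | 14.7 v 14.7 | 1.00 | 0.46 | 0.051 |
| B | 0.5 | 12.3 v 10.5 | 1.17 | 0.61 | 0.070 |
| B | 0.7 | 16.2 v 14.7 | 1.10 | 0.58 | 0.060 |
| C | 0.5 | 15.8 v 10.5 | 1.50 | 0.84 | 0.197 |
| C | 0.7 | 19.1 v 14.7 | 1.30 | 0.77 | 0.132 |

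P(more on intervention) is below one half in scenario A because ties are possible.

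**Reading.** Under scenario B the expected excess is about 1.5 to 1.8 affected participants (16.17 − 14.7 = 1.47; 12.25 − 10.5 = 1.75). Under scenario C it is 4.4 to 5.3 (19.11 − 14.7 = 4.41; 15.75 − 10.5 = 5.25). Events concentrated in the first month would move scenario B towards C.

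**The case against.** The strongest reply is that unequal contact is not the same as unequal elicitation. The stated content of the calls is adherence, with ease and subjective health change added at three months; no adverse-event question is described. Both arms are invited to a three-month GP assessment, and both see the same GP in ordinary care, so capture continues in both. The table is descriptive. The safety outcomes that are modelled, hospitalisation and long-term care admission, depend least on a telephone call. The calls are plausibly part of the intervention, since the feasibility study found higher compliance among people who had been called. Any bias in this direction is conservative for safety. The schedule of events is a figure that is not shown, and it may specify how adverse events are collected.

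Much of this stands, and it limits the point. A reader might infer that the table will show more events on intervention. The documents do not support that: the bias is zero if the calls recover nothing, and chance can reverse the direction in a single trial. A reader might also take 1.3-1.5 as the likely ratio. That needs the extra contact to cover events over the whole follow-up, which the one-month call cannot do. Nor can the plan be said to inflate a type I error for adverse events, because no such test is planned.

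The core remains. The intervention-only calls are in the text whatever the figure shows, the recording rule takes in anything reported on them, and the table as described pools events from every source.

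**Conclusion.** The concern holds as a risk of ascertainment bias in non-serious events. It is not a certain or measured distortion. The text combines unequal scheduled contact, recording that depends on contact, and by-arm tabulation without regard to source. The most plausible direction is more recorded events on intervention.

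A ratio of about 1.1-1.2 is the more defensible illustration, and 1.3-1.5 is the upper bound. Both rest on assumed detection of 50-70% per contact and equal true risk; the counts and probabilities in the table also rest on the assumed 20% risk with 105 per arm. The lower figure further assumes events spread evenly over three months. The consequence is for how a descriptive table reads. The primary outcome is not involved.

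**What to change.** Amend the Safety reporting and Safety analysis sections before three-month visits begin:

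1. At the existing three-month visit, put the same adverse-event question, covering the whole of follow-up, to every participant in both arms.
2. Base the main by-arm comparison on those answers plus events in the GP record, including hospitalisations.
3. Still report every event. Show those first disclosed at the intervention-only calls separately, labelled by source.

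The cost is one scripted question at a visit to which everyone is already invited, and a source field on the adverse-event form. The drawback is a longer recall period for mild events, which is the same in both arms. No safety information is lost and no visit is added.

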### Feasibility study

Feasibility of the exercise component of the intervention was assessed in a study in 2019 and 2020
^12^. The findings have been key to refining the intervention for this RCT. We offered an exercise intervention to reverse frailty and build resilience in primary care consultations. We set out to assess uptake of the exercise regime; ratings of its ease and subjective health after participation; how a follow-up telephone-call might affect compliance and overall feasibility. We applied the Bowen feasibility model
^13^ which has been successfully used in assessing public health and preventive medicine interventions. This feasibility model tests eight areas of focus: acceptability; demand; implementation; practicality; adaptation; integration; expansion; and limited-efficacy testing. Selected results include:

A total of 94 of 107 eligible people (88%) participated (average age 77, 59 females (63%)). 95% of females and 78% of males enrolled. Only 15% had previously considered resistance exercises.

Participants found the exercises both easy to follow and generally easy to do. Overall, 32% described exercises as ‘very easy’, 55% ‘somewhat easy’, 7% ‘neither easy nor hard’, 6% ‘somewhat hard and 0% ‘very hard’.

At one month, 66% of participants called were exercising regularly (76% of females, 50% of males). At two months, compliance among those who had not been called at one month was: 65% (67% of females, 62% of males). However, compliance among those previously called was higher: 78% (88% of females, 63% of males). 64% of those who were not doing exercises at one month had taken them up following the single phone call (67% of females, 63% of males).

Many described how the home-based exercises helped with staying active and reducing anxiety while housebound during the Covid-19 pandemic

The majority of participants self-reported their general health had improved as a result of doing the exercises and none reported feeling worse. 14% felt ‘much better’, 52% ‘slightly better’, 34% ‘about the same’, 0% ‘slightly worse’, and 0% ‘much worse’

Each of the eight areas of focus of the Bowen feasibility model have been addressed and satisfy overall feasibility. Publication of this feasibility study is pending.

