***Secondary outcomes***

 Clinical frailty status measured by CFS at three months after the start of intervention. Muscle mass measured by bioelectrical impedance at three months after the start of intervention.Body fat, bone weight, base metabolic rate, biological age by bioelectrical impedance at three months after the start of intervention. Incidence of in-patient hospitalisation during follow-up. Incidence of long-term care admission (LTC) during follow-up. Ease of the intervention measured on a five-point scale: ‘very easy’, ‘somewhat easy’, ‘neither easy nor hard’, ‘somewhat hard’, or ‘very hard’ three months after the start of intervention. Difference to general health as a result of the exercises measured on a five-point scale: ‘much better’, ‘slightly better’, ‘about the same’, ‘slightly worse’ or ‘much worse’ three months after the start of intervention.

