### Analysis sets

Final analysis for this trial will be conducted on the intention-to-treat population, which will include all subjects randomised to the treatment arms. Sensitivity analysis will be conducted on the per protocol population (full analysis set), which will include all subjects that attend all study visits and have complied with the intervention.

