### Procedure for accounting for missing, unused and spurious data

Where appropriate, missing data will be imputed using multivariate imputation by chained equations (van Buuren & Groothuis-Oudshoorn, 2011).

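### The three-month ease rating has no answer for participants who never started the exercises and no stated denominator, so it may describe mainly those who exercised.

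*Protocol article*

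**What the plan says.** The secondary objective is to learn how participants see the ease of the intervention and its benefit to their health. Two items under Secondary outcomes carry it: "Ease of the intervention measured on a five-point scale", and a five-point rating of difference to general health. Both answer lists are written out in full there and again under Study methods, assessments and procedures. Each has a neutral midpoint, two favourable and two unfavourable answers. Neither has a code for not having done the exercises.

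On collection, the methods section states: "Intervention participants will be called after one month and after three months by the GP". In these calls participants are "asked if they had followed the exercise regime (and for how long and how many times a week) and dietary guidance". The next sentence adds the ratings: "At three months they will be asked if they found the exercises" easy or hard, followed by the health question. The wording does not restrict the ratings to people who exercised, and it describes asking only the intervention arm.

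On analysis, the Efficacy analysis section fits a proportional odds model to both items with arm as covariate. The intention-to-treat population is one "which will include all subjects randomised to the treatment arms". The missing-data section says that, where appropriate, "missing data will be imputed using multivariate imputation by chained equations". No section says how a participant who did not exercise is to be rated or counted.

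**The concern.** Someone who never tried the exercises cannot say how easy they were. With only the five printed answers, that person is left blank or pushed into a category that does not apply. A blank can lead to a favourable picture by two routes. The person may drop out of the denominator. Or the blank may be treated as ordinary missing data and filled from people who did exercise, although a rating for a non-starter is undefined rather than missing. The withdrawal section adds to the first route: it lists lack of compliance among the reasons for which a subject must be withdrawn, so some non-exercisers may never reach the three-month question.

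The Introduction says the results are meant to encourage mainstream adoption in primary care. That needs a figure for everyone offered the programme. A figure for those who took it up answers a different question and will be read as answering the first.

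A second, softer concern is who asks. GP site investigators are trained both to deliver the intervention and to gather the data, so the person hearing the rating is likely to be linked to the advice being rated.

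**Working it through.** The plan gives no expected figure for either rating, so there is none to reproduce. What can be checked is how far the result could depend on the denominator.

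**Inputs**
- Feasibility study, ease: 32% very easy + 55% somewhat easy = 87%; the rest is 7% neutral, 6% somewhat hard, 0% very hard.
- Feasibility study, health: 14% much better + 52% slightly better = 66%; the rest is 34% about the same, 0% worse.
- Feasibility study, two-month compliance among people called earlier: a = 0.78. This is the closest match, because the trial calls every intervention participant at one month.
- Allocation: 210 enrolled 1:1, so about 210 / 2 = 105 in the intervention arm.

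**Assumption not in the document:** the feasibility ratings came only from compliant participants. The article does not state who was rated.

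**Formula.** Let r be the favourable share among compliant participants and q the share of the others who would count as favourable. The share of all allocated is a × r + (1 − a) × q.

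**Size of the group without compliance:** 1 − 0.78 = 0.22, and 0.22 × 105 = 23 participants.

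| Item | r | Share of all if q = 0 | Gap from r |
|---|---|---|---|
| Easy | 0.87 | 0.78 × 0.87 = 0.679 | 0.191 |
| Better | 0.66 | 0.78 × 0.66 = 0.515 | 0.145 |

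If q = r the gap is zero. On these inputs, the distance between the figure for exercisers and the figure for all allocated lies between 0 and about 19 points for ease, and between 0 and about 15 points for health, provided the others are no more favourable than the exercisers. The q = 0 row is the extreme end.

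**The two items behave differently.** A non-starter asked about health can truthfully choose the neutral answer. If all of them do, the 51% appears directly and the missing code causes no distortion. On ease, the neutral answer is still a statement about exercises the person did not do, so the item itself cannot produce the figure for everyone offered the programme.

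**Between-arm model.** The methods section describes the two questions for intervention participants only, and usual-care participants have no exercises to rate. With responses from one arm, the arm coefficient in the proportional odds model cannot be estimated.

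**The case against.** The strongest reply is that adherence is asked as well, so non-exercisers can be identified and cross-tabulated with their ratings, and that codes and denominators are details an article commonly leaves to the forms and the analysis plan. The first part stands: the information will exist. It does not close the gap, because the article fixes the answer list without a place for these participants and does not connect adherence to the rating.

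A reader might infer that both results are bound to be too favourable. The documents do not support that:
- Both scales are symmetric, and someone who stopped because the exercises were too hard can still choose a hard answer.
- On health, a non-starter who reports no change lowers the benefit figure.
- Imputation is qualified as applying where appropriate. Nothing says a non-starter's ease rating would be imputed, or that recorded adherence would be ignored.

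A reader might also put the uncovered group at up to 35%, using the lower feasibility figure: "compliance among those who had not been called at one month was: 65" per cent. That comes from people who received no one-month call, whereas this trial calls everyone. Nor is non-compliance the same as never starting: someone who exercises irregularly can rate ease. Three-month adherence is unknown.

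Finally, it is tempting to read the feasibility ease ratings, which add to 100% (32 + 55 + 7 + 6 + 0), as proof that non-exercisers were dropped. Any complete distribution adds to 100% whatever its denominator, so this shows nothing about who was rated.

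On the GP asking, the training sessions are meant to standardise patient communication and data gathering. Courtesy bias remains plausible, but its size cannot be computed from the documents.

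**Conclusion.** The point holds in a limited form. The ease item has no valid answer for participants who never started, and the article does not say how they enter the result. If they are left out, or filled in from exercisers, the ease figure describes mainly those who exercised and may overstate acceptability among everyone offered the programme. The health item is much less exposed.

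The drop from 87% to about 68% easy, and from 66% to about 51% better, shows how much the denominator can matter. It is not an estimate of bias. It rests on two-month compliance carrying over to three months, on an unstated feasibility denominator, and on scoring every non-compliant participant as not easy or not better.

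The one firm error is the between-arm model for questions described only for the intervention arm. All of this concerns subjective secondary outcomes. It is minor, though these two items are the ones that carry the stated secondary objective.

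**What to change.** 1. In Secondary outcomes and in Study methods, assessments and procedures, add two codes to both items: did not start, and stopped (with reason).
2. Report both ratings descriptively, with all participants allocated to the intervention as denominator and the two codes shown as separate categories.
3. State that ratings are not imputed for participants with either code.
4. In Efficacy analysis, replace the proportional odds model with arm as covariate for these two items by that within-arm description.
5. Preferably collect the answers on a short self-completed form at the three-month visit, keeping the telephone call for those who do not attend.

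The cost is two tick-boxes, one page per intervention participant and a few changed sentences. The headline ease figure is likely to look less favourable. The sample size and the primary analysis do not change.
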